**Fig. 1 Fig1:**
[figure not shown]
Plan of study

### Co-interventions

The following co-interventions are present in this study; supplementary nutrition, health education, pre-school non-formal education, immunisation, health check-up and referral services. These services are available to children in both the intervention and control arm as an inherent part of the ICDS scheme [13].

### Outcome variables

These will be assessed at enrollment, 6 months, 1 year, 2 years and 3 years after the start of the project. Personnel assessing the outcomes will be blinded to the group of intervention. The primary outcome variable will be change in dmfs count among 1 to 3-year-old children over a follow-up period of three years.

The secondary outcome variables will be:
individual child-level variables: dental caries count (caries reversals and caries increment), S mutans levels, Gingival and Plaque Indexmother and AWW-level variables: oral health-related KAP

Variables that will be measured at baseline and at each of the above time points are shown in Table 1.

**Table 1 Tab1:** Variables to be assessed during the study

Variables Assessment	Variable types	Data Analysis	Anticipated Outcomes	Time of measurement
At the level of the mother (Independent variables)				
Socio-Demographics	Continuous & Categorical	T-test and Chi-square tests.	Assess the distribution of population characteristics	At baseline
Health Literacy Levels	Continuous	T-test	Assess health-related literacy of the individual	At baseline
At the level of the child (Potential Confounders)				
Child Anthropometry (Weight & BMI)	Continuous	T-test	Assess BMI	At baseline and 6 months, 1 year, 2 years and 3-years post-intervention
Oral Health services utilisation	Categorical	Chi-square test	Assess the utilisation of dental care in the last 12 months	At baseline and 6 months, 1 year, 2 years and 3-years post-intervention
At the level of Mother and Anganwadi Worker (Outcomes)				
Oral Health-related KAP	Continuous & Categorical	T-test and Chi-square test	Assess the level of KAP related to oral health issues	At baseline and 6 months, 1 year 2 years and 3-years post-intervention
At the level of Child (Outcomes)				
Dental caries count	Continuous and Categorical	T-test and Chi-square test	Assess the level of dental caries status	At baseline and 6 months, 1 year and 3-years post-intervention
S. mutans levels	Continuous and Categorical	T-test and Chi-square test	Assess the level of dental caries causing organisms	At baseline and 6 months, 1 year and 3-years post-intervention
Gingival and Plaque Index	Continuous and Categorical	T-test and Chi-square test	Assess the level of oral hygiene	At baseline and 6 months, 1 year and 3-years post-intervention

### Plan for analysis

As the population of children in an AWC is not stable, with older children who cross 6 years of age leaving the AWC and young children joining the AWC; two types of analysis have been planned. The primary analysis will be an inter-group comparison of a stable cohort of children aged 1 to 3 years who will be recruited at the beginning of the study and shall be followed up for 3 years until the age of 4 to 6 years respectively. The secondary analysis will be a cross-sectional inter-group comparison of all available children aged 1 to 6 years present at follow up evaluations (6 months, 1 year, 2 year and 3 years). Children in the secondary analysis will have varying points of entry and different durations of follow-up. All the above-listed outcome variables will be analysed both in the primary and the secondary analysis.

The primary analysis will be done on an intention-to-treat basis. Qualitative data shall be expressed using frequency distribution and percentages, whereas quantitative data shall be expressed as mean (standard deviation) or median (1st, 3rd quartile) depending upon distribution. Normality of distribution will be assessed by Shapiro Wilk test and Q-Q plot. Qualitative variables will be compared between the two groups by chi-square test or Fisher’s exact test, as appropriate. Quantitative variables will be compared between the two groups by Student’s t-test or Mann-Whitney U test, depending upon distribution. Repeated measures analysis between the two groups will be performed using two-way repeated-measures ANOVA or mixed linear models or generalised estimating equations, depending upon the variable and statistical assumptions.

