**Discussion:**

ECC prevention had conventionally focused upon testing effectiveness of programs targeting behaviour change among the caregivers and children, but surprisingly minimal efforts have been made to seek translation of these efforts into reduction of ECC at the community level. The present study has two components; testing effect of altering maternal and child behavioral aspects on ECC incidence through cohort follow up of 1–3-year-old children for three consecutive years and cross-sectional follow up of all available 1–6-year old children at the selected AWCs at regular intervals to look for change in prevalence of ECC at community level. In other regions of the world surveys of ECC prevalence before and after the intensive educational programs have shown a significant reduction in ECC prevalence. A similar decline can be anticipated through this program.

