ECC prevention had conventionally focused upon testing effectiveness of programs targeting behaviour change among the caregivers and children, but surprisingly minimal efforts have had been made to seek translation of these efforts into the reduction of ECC at the community level. The present study shall simultaneously carry with it both the components, i.e. testing effect of altering maternal and child behavioral aspects on ECC incidence through Cohort follow up of 1–3-year-old children for three consecutive years and also a cross-sectional follow up of all available 1–6-year old children at the selected AWCs at regular intervals to look for any change in prevalence of ECC at community level. In other regions of the world surveys of ECC prevalence before and after the intensive educational programs have shown a significant reduction in ECC prevalence [22–27]. A similar decline can be anticipated through this program as well.

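### The community-level secondary analysis compares arms at follow-up surveys only, although its purpose is change in ECC prevalence and baseline outcomes are collected; existing block differences carry into the apparent effect

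*Protocol article*

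**What the plan says.** Under Plan for analysis, the protocol article separates a primary analysis (a closed cohort recruited at age 1 to 3) from a secondary one in an open population. Of the latter it says: "The secondary analysis will be a cross-sectional inter-group comparison of all available children aged 1 to 6 years present at follow up evaluations". The surveys are then listed: "present at follow up evaluations (6 months, 1 year, 2 year and 3 years". Enrollment is not among them. The section adds: "Children in the secondary analysis will have varying points of entry and different durations of follow-up".

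The tests named for two-group comparisons are chi-square or Fisher's exact for categorical variables and Student's t or Mann-Whitney for quantitative ones. A further sentence provides for repeated-measures analysis between groups by two-way ANOVA, mixed linear models or GEE. It names neither the secondary analysis nor baseline.

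The purpose is worded as change. The abstract says the cross-sectional component is there "at regular intervals to look for change in prevalence of ECC at community level", and the main Discussion repeats this: "to look for any change in prevalence of ECC at community level". The Discussion supports the expected decline with before-and-after evidence: "surveys of ECC prevalence before and after the intensive educational programs have shown a significant reduction in ECC prevalence".

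Baseline data will exist. Outcome variables says: "These will be assessed at enrollment, 6 months, 1 year, 2 years and 3 years after the start of the project". Table 1 lists baseline for the dental caries count, and the eligibility section covers children aged 0 to 6 years.

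Under Study design, each of the two sites contributes two geographically distant ICDS blocks, one randomised to each arm: four units of allocation in all.

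**The concern.** A between-arm comparison at follow-up estimates a difference in level. The stated question is about change. The two coincide only if the arms start level, and with one block per arm per site nothing in the design makes that likely. The blocks are also chosen to be far apart, which helps against contamination but gives no reason to expect equal starting prevalence.

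If prevalence already differs between the blocks, a follow-up-only test can report that difference as an effect or hide a real effect of opposite sign. This is one of the study's two stated components, and the article contemplates extending the programme to other centres if it is found effective.

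**Working it through.** **The plan's own figure.** For the primary outcome, Sample size estimation gives about 605 per arm from SDs 14.3 and 16.3, difference 2.47, 5% alpha and 80% power. The check is (1.960 + 0.842)² × (14.3² + 16.3²) / 2.47² = 7.849 × 470.18 / 6.101 = 604.9, so it reproduces. The point here does not depend on it. The inflated figure of 950 per arm per centre is used below as the size of a survey. The article gives no separate count for the cross-sections, but 40 centres × 25 children = 1,000 is close.

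**What each contrast estimates.** Let D be the starting difference in prevalence between two blocks at a site, E the true effect, and S any block-specific drift over time.

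- Follow-up only: D + E + S + sampling error.
- Difference in change from baseline: E + S + sampling error.

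Only the second is free of D.

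**Size at one site.** Inputs: 950 per arm; prevalence centred on 60%, the middle of the 50 to 70% quoted in Background for Indian children under 5; E = 0; S = 0. D is an assumption.

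- Null standard error: √(2 × 0.6 × 0.4 / 950) = 0.0225.
- Two-sided 5% critical difference: 1.96 × 0.0225 = 0.044.
- For D = 0.02, the true prevalences are 0.59 and 0.61. The upper tail is 1 − Φ((0.044 − 0.02) / 0.0225) = 1 − Φ(1.07) ≈ 0.142. The lower tail adds about 0.002, giving 0.144.

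| Assumed starting gap (points) | Significant, no true effect: one site, 950 per arm | Both sites pooled, 1,900 per arm, gap in the same direction |
|---|---|---|
| 0 | 5% | 5% |
| 2 | 14% | 24% |
| 3 | 27% | 47% |
| 5 | 60% | 88% |

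**When the direction of the gap is left to chance.** A simulation drew block prevalences at random around 60% (two sites, one block per arm per site, 950 children per block per survey, no true effect) and averaged the site differences. Between-block SD and drift SD are assumptions.

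| Between-block SD (points) | Drift SD (points) | Follow-up-only rejects | Change-from-baseline rejects |
|---|---|---|---|
| 0 | 0 | 5% | 5% |
| 2 | 0 | 22% | 5% |
| 3 | 0 | 36% | 5% |
| 5 | 0 | 56% | 5% |
| 2 to 5 | 1 | 26 to 56% | about 7% |
| 2 to 5 | 2 | 34 to 58% | 14 to 15% |

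Centring on 50% or 70% gives similar results.

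**Cost in precision.** If two independent surveys are simply subtracted, the variance doubles: √(4 × 0.6 × 0.4 / 950) = 0.0318 against 0.0225, a ratio of 1.41. Children seen at both surveys would normally be positively correlated, which lowers it.

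**The case against.** The best defence is the repeated-measures sentence. All listed outcomes are to be analysed in both the primary and the secondary analysis, those outcomes are measured at enrollment, and a GEE or mixed model with an arm-by-time term would fit that text. The list of follow-up visits could be read as saying who is surveyed rather than what enters the model. This has some force: baseline is not excluded. But the sentence assigns no baseline-referenced model to this analysis, one of its options (repeated-measures ANOVA) does not suit a population whose members change between surveys, and the only contrast defined for the secondary analysis is at follow-up.

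A second defence is that model terms belong in an analysis plan not shown here. That holds for age, site and clustering terms, whose absence is not the point. It does not hold for the population, contrast and time points, which the article itself fixes.

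Third, blocks are randomly allocated. A reader might infer that the follow-up comparison is systematically biased, and the documents do not support that: over repeated allocation, chance imbalance averages out. What remains is that in the single allocation carried out the imbalance is present, and the named tests have no term for it, so the error is understated.

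Other stronger readings also fail. The 50 to 70% range describes Indian children generally and is not evidence of a gap of, say, 10 points between two blocks at one site. Mixed exposure is disclosed, suits a community-level question, and dilutes an effect rather than creating one. Age distorts the contrast only if the age mix differs between arms, which nothing in the article shows.

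**Conclusion.** The point stands for the secondary analysis as written. Its stated purpose is change in prevalence, its defined contrast is a difference in level at follow-up, and the baseline that would link the two is collected but not assigned to it. With one block per arm per site, any starting difference enters the result in full.

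How much this matters depends on a between-block difference that the documents do not give. The rates of 14%, 27% and 60% for gaps of 2, 3 and 5 points are conditional on those assumed gaps, on 950 children per arm at one site and on prevalence near 60%; they are not predictions.

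A reader might conclude that the trial cannot show change in prevalence at all. That goes too far: the limitation lies in the comparison as defined, not in the data. The plan should be changed, and easily can be. The point does not touch the primary cohort comparison.

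**What to change.** Amend Plan for analysis so that the secondary analysis includes the enrollment cross-section of 1 to 6-year-olds, and make the arm-by-period contrast the secondary estimate: change in ECC prevalence from baseline, compared between arms within site and combined across sites. Adjust for age band and fit it, for example, by a mixed model or GEE that allows for clustering within Anganwadi centres. State that this model, rather than repeated-measures ANOVA, applies to the open population. Present the comparisons at each follow-up survey descriptively.

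Use baseline once. Adding each centre's baseline prevalence as a covariate on top of the change contrast would use it twice, and with about 25 children per centre that covariate has a standard error of about √(0.6 × 0.4 / 25) = 0.098, or 10 points.

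The cost is some precision: a standard error up to about 1.4 times larger, with no new data collection. The change removes stable block differences only. Block-specific drift and inference from four clusters remain, and the plan should state both as limitations of this analysis.

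### The secondary cross-sectional comparison pools ages 1 to 6 with tests that ignore age, so a difference in age mix between blocks can pass for a difference in caries

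*Protocol article*

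**What the plan says.** The Plan for analysis sets out two analyses. The primary one follows "a stable cohort of children aged 1 to 3 years who will be recruited at the beginning of the study", who "shall be followed up for 3 years until the age of 4 to 6 years respectively". The other is described thus: "The secondary analysis will be a cross-sectional inter-group comparison of all available children aged 1 to 6 years present at follow up evaluations". The stated reason for having two is an unstable population, with "older children who cross 6 years of age leaving the AWC and young children joining the AWC". The article discloses one limitation of the second analysis: "Children in the secondary analysis will have varying points of entry and different durations of follow-up". It also says: "All the above-listed outcome variables will be analysed both in the primary and the secondary analysis".

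For comparisons between two groups, the same section names Student's t-test or Mann-Whitney for quantitative variables and chi-square or Fisher's exact test for qualitative ones. Table 1 lists t-test and chi-square against dental caries count. Repeated-measures ANOVA, mixed models and GEE are offered for repeated-measures analysis, with no covariates named. No age strata, age adjustment or standardisation is mentioned for the cross-section.

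Measurement of variables lists the child's age among the demographic variables and potential confounders recorded at enrolment. Study design states that only two large clusters per site are compared, one per arm. The Discussion gives the cross-section its purpose: "to look for any change in prevalence of ECC at community level".

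**The concern.** The dmfs count is cumulative. The source study used in Sample size estimation saw mean rises of 11 and 13.47 over two years, so a child's age strongly affects the count. Pooling five or six years of age makes the arm mean, or the arm prevalence, depend on how many older children happen to attend.

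With many small clusters, randomisation would tend to even this out. With one block per arm at each site it cannot be relied on to do so: any difference in age structure between two distant blocks goes straight into the comparison, in either direction. Because children join and leave, the mix can also drift between surveys. What is at stake is the statement about community prevalence, which a reader could take for an effect of the package when part of it is age composition.

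**Working it through.** The plan gives no age distribution, no age-specific prevalence and no figure for the overlap between the two analyses, so there is nothing of its own to reproduce on this point. Its target difference serves below as a yardstick. That figure is internally consistent: 13.47 − 11 = 2.47, and (1.960 + 0.842)² × (14.3² + 16.3²) / 2.47² = 604.9, against the stated 605.

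**1. Age mix and prevalence.** Split the children into a younger group (under 4) and an older group (aged 4 to 6).

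Spurious difference = (difference between blocks in the share aged 4 to 6) × (older prevalence − younger prevalence).

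All inputs are assumptions: a share difference of 5, 10 or 15 points, and two prevalence pairs.

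- 50% and 70%: 0.05 × 0.20 = 0.01, 0.10 × 0.20 = 0.02, 0.15 × 0.20 = 0.03, that is 1 to 3 points.
- 25% and 65%: 0.05 × 0.40 = 0.02, 0.10 × 0.40 = 0.04, 0.15 × 0.40 = 0.06, that is 2 to 6 points.

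The Background puts prevalence below age 5 at 50 to 70%. With uniform ages from 1 to under 5, the first pair implies (3 × 50 + 70)/4 = 55%, inside that range. The second implies (3 × 25 + 65)/4 = 35%, below it. The first pair therefore fits the article better, and the second shows a steeper age gradient.

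**2. Age mix and dmfs.** Spurious difference = (dmfs gained per year of age) × (difference in mean age). Assume 1 to 6.7 dmfs per year, the upper value being 13.47/2 from the control arm of the source study, and a difference in mean age of 0.25 years.

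- 1 × 0.25 = 0.25, or 0.25/2.47 = 10% of the target difference.
- 6.7 × 0.25 = 1.7, or 68% of it.

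**3. Overlap with the cohort.** Cohort children still attending at a survey meet the definition of the cross-section. With uniform ages, full enrolment and no loss, their share is (width of the cohort's age band at that survey, cut at the exit age) / (width of the surveyed band).

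| Reading of the age bands | 6 months, 1 and 2 years | 3 years |
|---|---|---|
| Entry at exact ages 1 to 3, survey 1 to 6 | 2/5 = 40% | 2/5 = 40% |
| Entry in completed years 1 to 3, exit at sixth birthday | 3/5 = 60% | 2/5 = 40% |
| Entry in completed years 1 to 3, exit at seventh birthday | 3/6 = 50% | 3/6 = 50% |

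Attrition lowers these shares. At 3 years with 80% retention (assumed), the lowest case is 0.40 × 0.80 = 32%, where lost children are replaced by others of the same age. The highest is 3 × 0.80 / (3 × 0.80 + 3) = 44%, where they are not replaced. With retention of 605/950 = 64%, the same formulas give about 25% to 39%.

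**The case against.** The strongest reply is that model covariates belong in a statistical analysis plan or the full protocol, neither of which is shown, and that the article lists age as a potential confounder and allows mixed models and GEE. This stands in part: age adjustment may be planned elsewhere, and it would be wrong to infer that the investigators mean to ignore age. But the article does name its two-group tests, and those cannot carry age. The models that could are tied to repeated measures.

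A second reply is that a constant difference in age mix would largely cancel if arms were compared on change from baseline. That is fair. However, the stated analysis compares groups at the follow-up surveys, and a mix that drifts would not cancel.

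A reader might also infer that the cross-section is offered as independent evidence and that the overlap is therefore an error. The article does not support this. It labels the analysis secondary, gives it a different target and never calls it independent. A survey of the community properly includes the cohort children, who belong to it. Nor is an overlap of 40 to 60% a property of the plan: it rests on uniform ages and no loss, and 60% arises on one reading only, up to year 2.

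Finally, one might want to rest the community statement on children outside the cohort. That would change the target. It would also move the analysed group from mainly older children at 6 months to mainly younger ones at 3 years. Dropping 40 to 60% of the sample would raise the standard error by 1/√0.60 − 1 = 29% to 1/√0.40 − 1 = 58%.

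**Conclusion.** The point holds as a weakness in the stated method of a secondary analysis. An age-dependent outcome is pooled over ages 1 to 6 and compared by tests that take no account of age, in a design that cannot be relied on to balance age between arms. The primary cohort analysis is not affected by this point.

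The size is not known. The 1 to 3 or 2 to 6 prevalence points, and the 10 to 68% of the target dmfs difference, depend on assumed age gradients and assumed differences between blocks. They show that the risk is not negligible, not that a bias of that size exists.

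The overlap is a matter of interpretation only. Since the cross-section includes the cohort children who still attend, and uses the same blocks and outcomes, agreement between the two analyses should not be read as independent confirmation.

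**What to change.** In the Plan for analysis, under the secondary analysis, state three things.

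- At each survey, arms are compared within one-year age bands or in a model adjusted for age.
- The pooled figure for ages 1 to 6 is standardised to one fixed age distribution, named in advance and used for both arms and all surveys.
- The cross-section includes cohort children still attending, with their number given at each survey. Results for cohort and non-cohort children may be shown side by side as description, but the community estimate remains that of all children surveyed.

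Align the caries row of Table 1 with this.

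Age is already recorded and cohort membership is known from enrolment, so the cost is analysis work, with no new data. If the 25 children per centre span ages 1 to 6 (the article does not say), 40 × 25 = 1000 children per arm and site give about 1000/6 = 167 to 1000/5 = 200 per one-year band. The bands would then be usable, though less precise singly than the pooled figure. Age adjustment removes only the age component; other differences between single blocks remain.

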
Prevention of ECC can be brought through education of expectant mothers and mothers of young children regarding appropriate oral hygiene measures and dietary practices. In a utopian universe, this task would best be carried out by trained dental professionals. However, the country faces a gross disparity in the regional distribution of the dental health workforce, as mentioned before. A promising alternative workforce for the task seems to be the female workers at the Anganwadi centres (AWC) under the ICDS scheme which was launched in 1975 to provide mid-day meal, pre-school education and primary healthcare to children under 6 years of age. These workers can be used to effectively counsel and deliver the oral health education to both children and mothers’ thus serving as the much-needed initiative at the national level. ICDS scheme is an ideal example of community participation under the Primary Health Care concept (Alma Ata declaration 1978). As of 2015, the number of operational AWCs in India is 1,349,091 with each centre covering a population of 1000 in rural and urban areas and 700 in Tribal regions [13]. Anganwadi workers (AWW) promote and monitor overall child development, carry out additional feeding, immunisation, dispense vitamin A, iron and folic acid tablets and referral to the medical care facility. AWWs also provide outreach services by visiting door-to-door in the community as agents of social change mobilisation for better care of young children, girls and women. Though adequately trained on issues concerning general health, various studies have cited limited oral health knowledge and awareness among them [14, 15]. Nevertheless, they appear to be a potential health workforce that is yet to be utilised for controlling and limiting many prevalent oral diseases like ECC in India.

A one-year pilot project funded by the Department of Science and Technology, Government of India (2014–15), was carried out to develop an oral health care package for prevention and control of oral diseases among mothers and pre-school children, and to test whether AWWs could be utilised for delivering this package.

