### Study participants, study setting and subject eligibility criteria

Children aged 0–6 years and their mothers attending AWCs shall constitute the study population. Expectant mothers and mother-child pair of children aged 0–6 years enrolled at the selected AWCs and who agree to participate in the study will constitute the study sample. Study subjects will be excluded if theyare found to be already enrolled with any other trial related to oral health care.

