#### Application of 2.26% fluoride varnish and 10% Povidone-iodine

2.26% fluoride varnish and 10% Povidone-iodine will be topically applied to the teeth of children aged 1–6 years, once every 3 months, by a dentist in the same appointment

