### Sample size estimation

Sample size calculation for the study has been based upon a similar study conducted by Lawrence HP et al., 2008 for prevention of dental caries among aboriginal children in Canada, with 2-year, follow up [18]. In the above study, the mean (SD) change of dmfs in intervention and control arm was 11 (14.3) and 13.47 (16.3), respectively, resulting in a mean difference of 2.47.

Assuming a 5% alpha error and 20% beta error, to detect a mean difference with standard deviations as above, using the sample size formula (z_1-α/2_ + z_1-β_)^2^ x (σ_1_^2^ + σ_2_^2^)/(μ_1_-μ_2_)^2^, the required sample size has been calculated to be approximately 605 in each arm. The design effect due to clustering has not been included, because we do not have prior information about the intra-class correlation within a cluster. To account for an attrition in the number of study subjects, and to account for a decrease in the effect size (due to a potential waning in the performance of AWWs in the intervention clusters over the three-year study period, and a possible Hawthorne effect) it was decided to inflate the sample size approximately 1.5 times, resulting in 950subjects in each arm at each study center (Chandigarh and Cuttack). On average, around 25 children are attached to each AWC. Therefore, at each study centre, a cluster of 40 AWCs will be selected within each of the two ICDS blocks, and the blocks will be randomly located to the intervention and the control arm.

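### The cross-sectional survey describes children at the selected AWCs, not ECC prevalence in the community, and its make-up could come to differ by arm

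*Protocol article*

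**What the plan says.** The Discussion (and, in similar terms, the abstract) names two components. One is the cohort. The other is a "cross-sectional follow up of all available 1–6-year old children at the selected AWCs at regular intervals", whose purpose is "to look for any change in prevalence of ECC at community level".

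The Plan for analysis makes this the secondary analysis and describes it as a "cross-sectional inter-group comparison of all available children aged 1 to 6 years present at follow up evaluations", at 6 months and at 1, 2 and 3 years. It says that the AWC population is not stable, because older children leave and younger ones join, and that surveyed children will differ in entry point and length of follow-up. The eligibility section restricts the sample to those "enrolled at the selected AWCs and who agree to participate in the study".

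On coverage, the Background describes AWCs "with each centre covering a population of 1000 in rural and urban areas", and 700 in tribal regions. Sample size estimation says that "around 25 children are attached to each AWC".

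The arms offer different things at the centre. In Group I, varnish and povidone-iodine are applied "once every 3 months, by a dentist in the same appointment", AWWs are trained to educate mothers, and mothers may subscribe to weekly SMS. Group II has the usual basic hygiene advice.

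**The concern.** There are two separate problems.

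The first is the target. A survey of enrolled children found at an AWC gives prevalence among those children. It gives community prevalence only if children who are not enrolled have the same prevalence, and nothing in the article allows that to be checked. No catchment denominator and no comparison with children outside the AWC is described. A later analysis cannot repair this, because the missing children are never examined.

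The second is the comparison between arms. Membership of each survey round is settled after the blocks are allocated, while the centres offer different services. Families in Group I have an added reason to join or attend. If they respond to it, a difference in surveyed prevalence mixes the effect of the package with a change in who is surveyed. The sign is open. Families of diseased children may come for the dentist, which would hide a benefit. More health-minded families may come for the programme, which would exaggerate one. Blinded assessors and random allocation do not prevent this, because neither governs who enters the sample afterwards.

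At stake is the conclusion from one of the two stated components, in a project whose results may go to policymakers.

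**Working it through.** **The plan's own figure.** The article gives no sample size or coverage figure for the survey. Its 605 per arm is for the dmfs outcome and reproduces: (1.960 + 0.842)² × (14.3² + 16.3²) / 2.47² = 604.9. It does not bear on this point. The survey would hold about 40 AWCs × 25 children = 1000 per arm per site.

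**Step 1: coverage.** From the article: 25 attached children per AWC, and a catchment of 1000 or 700 people. Not in the article: the share of the population aged 1–6. I assume 10–14%, with a wider range of 6–14%. Coverage = 25 / (catchment × share).

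| Share aged 1–6 (assumed) | Catchment 1000 | Catchment 700 |
|---|---|---|
| 6% | 25/60 = 42% | 25/42 = 60% |
| 8% | 25/80 = 31% | 25/56 = 45% |
| 10% | 25/100 = 25% | 25/70 = 36% |
| 12% | 25/120 = 21% | 25/84 = 30% |
| 14% | 25/140 = 18% | 25/98 = 26% |

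If 25 counts all attached 1–6-year-olds, at least 40% of those eligible are outside the survey in every cell.

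**Step 2: distance from community prevalence.** With coverage c, prevalence pA inside the survey and pN outside it, community prevalence is c·pA + (1 − c)·pN. Surveyed minus community prevalence is therefore −(1 − c)(pN − pA). At c = 25%:
- a gap of 10 points between those outside and inside gives −0.75 × 10 = −7.5 points;
- a gap of 20 points gives −15 points;
- no gap gives 0.

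The article gives no such gap, so these values are illustrations.

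**Step 3: possible difference between arms with no true effect.** If coverage rises from c0 to c1 in one arm only, and newcomers differ from usual attenders by g, the spurious difference is g × (c1 − c0)/c1. From 25% to 35% the factor is 0.10/0.35 = 0.286:
- g = 10 points gives 2.9 points;
- g = 20 points gives 5.7 points;
- unchanged coverage gives 0, whatever g is.

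Take a control prevalence of 60% (inside the article's 50–70%), hold 1000 children per arm, treat children as independent, and let newcomers have less disease. A two-sided 5% test of 60% against 57.1% or 54.3% would then be significant in about 25% or 73% of trials. The attendance change and g are invented inputs. The result shows that a moderate shift could matter, not that one will occur.

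**The case against.** The strongest case against is that the article already discloses the scope. The Discussion sentence that mentions the community also places the survey at the selected AWCs, the eligibility section speaks of children attending AWCs, and upscaling is discussed only for other AWCs. The analysis is labelled secondary, with a warning about varying entry and follow-up. This lowers the severity, but it leaves a stated purpose that the sample cannot serve.

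A reader might infer that the two arms' samples will drift apart. The documents do not support that. The only movement they describe is by age, and it operates in both arms. Both arms also have outcome examinations and the ICDS services, and referral cards are not limited to one arm. The rural dentist ratio of 1:30,000 in the Background does not describe peri-urban Chandigarh. What stands is a risk, not a fact.

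A reader might also infer that the survey covers only a small share of children. That depends on an age share the article does not give. The meaning of 25 is open too, because it is used to convert a sample size for the 1–3-year-old outcome into AWCs. If it counts only children of cohort age, and 1–6-year-olds number about 50 per AWC, coverage at age shares of 8–12% would be 42–63% (50/120 to 50/80), or 60–89% in a catchment of 700 (50/84 to 50/56). A minority is probable, not established.

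Finally, being present may mean being on the roll at that round, not in the room that day. This narrows the attendance route. The enrolment route and the gap between AWC and catchment remain.

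**Conclusion.** The point holds in a limited form. The claim about prevalence in the community does not follow from a sample of enrolled, consenting children available at the selected AWCs, and no analysis of those children can supply it. This conclusion rests on the article's text alone. That the sample is a minority of eligible children rests on the assumed age share and on 25 counting all attached 1–6-year-olds.

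A change in composition that differs by arm is a real possibility, because the population is open and the services differ. Its size and sign are unknown, and it is zero if attendance does not respond to the package. The 2.9–5.7 points above are an illustration and not an estimate.

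The primary comparison, in the cohort recruited at the start, is not touched. I rate the point minor to moderate: it changes what the secondary analysis may conclude.

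**What to change.** 1. In the abstract and the Discussion, restrict the conclusion of the cross-sectional component to children enrolled at or attending the selected AWCs.
2. In the Plan for analysis, define the survey denominator as children aged 1–6 on the AWC roll at each round, by the same rule in both arms.
3. Report the numbers enrolled and examined, by arm and round.
4. Show results separately for children on the roll at baseline and for later joiners, by arm, as a check on changed composition.

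The cost is one or two extra tables and a narrower claim. No further examinations are needed. I do not propose sampling from households in the catchment. It would bring in children outside the stated eligibility, who would need tracing and consent, and the article mentions no household list to draw from.
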